## Abstract

**Background:**

Cerebral palsy is a permanent disorder of posture and movement caused by disturbances in the developing brain. It affects approximately 1 in every 500 children in developed countries and is the most common form of childhood physical disability. People with cerebral palsy may also have problems with speech, vision and hearing, intellectual difficulties and epilepsy. Health and therapy services are frequently required throughout life, and this care should be effective and evidence informed; however, accessing and adopting new research findings into day-to-day clinical practice is often delayed.

**Methods/Design:**

This 3-year study employs a before and after design to evaluate if a multi-strategy intervention can improve research implementation among allied health professionals (AHPs) who work with children and young people with cerebral palsy and to establish if children’s health outcomes can be improved by routine clinical assessment. The intervention comprises (1) knowledge brokering with AHPs, (2) access to an online research evidence library, (3) provision of negotiated evidence-based training and education, and (4) routine use of evidence-based measures with children and young people aged 3–18 years with cerebral palsy. The study is being implemented in four organisations, with a fifth organisation acting as a comparison site, across four Australian states. Effectiveness will be assessed using questionnaires completed by AHPs at baseline, 6, 12 and 24 months, and by monitoring the extent of use of evidence-based measures. Children’s health outcomes will be evaluated by longitudinal analyses.

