### Overall purpose and hypotheses

This study aims to *improve allied health professional research implementation behaviours* using a tailored multi-strategy intervention package [33] and to reduce the research-practice gap in multiple organisations that provide services to children with cerebral palsy.

Our specific research questions includeDoes the tailored multi-strategy intervention change AHP behaviours via greater use of evidence-based outcome measures and/or interventions, and improved AHP knowledge of evidence-based interventions and outcome measures for children with cerebral palsy?How does AHP knowledge of evidence-based interventions and outcome measures for children with cerebral palsy in the four organisations in which the intervention is introduced compare to the organisation in which the practices are mandated?What is the relationship between the numbers and/or type of barriers to knowledge translation and the level of uptake of routine use of outcome measures in different healthcare organisations?How do barriers in the four organisations in which the intervention is introduced compare to the organisation in which the practices are mandated?How does the size and scope of the organisation impact the implementation of the multi-strategy approach?Do time trends show a reduction in rates of adverse outcomes, including severe scoliosis, hip dislocation (MP >100%) and progressive limb contractures over the study period, for children with cerebral palsy whose parents consent to be a part of this project? If so, are these trends comparable to Swedish cerebral palsy follow-up outcomes?

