## Methods/design

### Research design

This study will employ a before and after design [35] in four Australian non-government organisations that provide allied health services to children with cerebral palsy, with a fifth organisation acting as a comparison site. Included organisations are Yooralla and Kids Plus in Victoria, St Giles in Tasmania, Novita Children’s Services in South Australia and Cerebral Palsy Alliance in New South Wales. Cerebral Palsy Alliance will act as a comparison site as the tailored intervention is mandated in that organisation and embedded in routine practice following a randomised controlled trial [33]. By mandating these practices, the Cerebral Palsy Alliance is deemed to be operating according to the ‘make it happen’ concept ([34], p. 593). Having a comparison site in which the tailored intervention is in routine use affords the opportunity to examine the process of diffusion of innovation and describe features that may account for the success or failure of the tailored intervention in different organisations, as recommended by Greenhalgh et al. ([34], p. 615–6), and articulated in research questions two and three above. Measures of clinician practices at each site will be collected at baseline (prior to implementation of the intervention) and at 6, 12 and 24 months following implementation. The total study duration is 3 years.

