### Intervention

The tailored multi-strategy intervention aims to address known barriers to evidence use and will consist of:Identification of ‘*Knowledge Brokers*’ (expert research translators) based at each organisation who will aim to redress workplace barriers unique to each site. Each organisation will nominate one or more knowledge brokers for their site who has demonstrated leadership skills, excellent communication skills, peer respect and a specific interest in evidence-based practice. The knowledge brokers will work with the project team, the organisation’s management and the AHPs to act as agents in the process of translating and contextualising evidence for users within the organisation. This will involve taking part in training and cross-organisational knowledge broker support groups to develop the knowledge brokering role, identifying facilitators and ameliorating context-specific barriers, contributing to the delivery of education packages and providing day-to-day support to AHPs as they engage in project activities and outcomes.Provision of a *customised e-evidence library*—‘*CP Decision*’ [36]—to enable AHPs rapid and real-time access to synthesised and critiqued cerebral palsy research evidence. This library employs a traffic light system corresponding to evidence levels [21] and will be updated on an ongoing basis to accommodate new evidence as it emerges. The resource also contains a suite of decision-making intervention algorithms based on best available evidence in addition to research on cerebral palsy prognosis and assessment. The purpose of providing *CP Decision* is to decrease the amount of time it takes AHPs to retrieve the highest levels of published evidence.*Negotiated education and professional development days* for AHPs at partner organisations (implemented by the project investigators and the organisation-based knowledge brokers) about ‘how to’ implement or administer the current and most effective treatment and measurement options for cerebral palsy, using concrete and precise descriptions of the clinical processes involved.Provision of an *electronic cerebral palsy clinical outcomes database* (CP Check-Up™, provided by Cerebral Palsy Alliance). This electronic tool will be used by AHPs to record routine valid and reliable clinical measurements of participating children and to summarise the therapeutic interventions provided to these children. Through instant generation of an electronic report, the tool will provide real-time feedback about changes in outcomes of individual children over time, guiding evidence-based clinical decision-making to support direct therapeutic intervention and timely referral to ancillary services.

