*Change in AHP evidence-based practice knowledge* (research question 1) will be measured using the Evidence Based Practice and Outcome Measurement Competency quiz [33] that has been integrated into the Best Service Best Time Evaluation for the purposes of this study. This knowledge quiz includes open-ended questions developed by a panel of experts and assesses AHP’s knowledge of reliable, valid measures used in cerebral palsy and the current level of evidence for interventions used for children with cerebral palsy. This measure will be implemented at baseline, 6, 12 and 24 months.

*Impact of organisational factors on implementing the strategies* (research questions 2 and 3) will be assessed using mixed methods, including a questionnaire that evaluates AHP perception of the extent to which organisational factors act as supports or barriers to implementation of evidence-based practices (Supports and Barriers Questionnaire, adapted with permission from [38]) and qualitatively through focus groups and interviews. Focus groups will include three groups of participants, each with representatives from the participating organisations: (1) knowledge brokers, (2) clinical services managers and (3) participating AHPs. Interviews will be conducted with senior managers or chief executive officers.

*Longitudinal outcomes of children with cerebral palsy* (research question 4) will be assessed using clinical data extracted from the clinical outcomes database. Specific musculoskeletal measurements will be modelled from data collected at 6, 12 and 24 months.

Additional data relating to potential confounders for uptake of evidence-based practices will be collected including organisational characteristics such as profile of children attending the service (multiple diagnoses or only cerebral palsy), size and number of sites that an organisation operates from and professional characteristics of AHPs including discipline, years of experience and proportion with higher degrees. In addition, a record of implementation at each site, including number and timing of recruitment of knowledge brokers and staff, days and topics of professional development provided and frequency of hits (number of times accessed) on the e-library, will be kept to provide process measures for the study.

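### The abstract promises to establish that routine assessment improves child outcomes, but the design has no course over time without routine assessment, and the child model does not name the baseline visit

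*Protocol article*

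**What the plan says.** The Methods/Design paragraph of the abstract gives the child-level aim as "to establish if children’s health outcomes can be improved by routine clinical assessment". It lists as the fourth intervention component "routine use of evidence-based measures with children and young people aged 3–18 years with cerebral palsy".

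The Intervention section describes the clinical outcomes database: "This electronic tool will be used by AHPs to record routine valid and reliable clinical measurements of participating children". Under Outcome measures, the children's longitudinal outcomes "will be assessed using clinical data extracted from the clinical outcomes database", and musculoskeletal measurements are to be modelled from 6, 12 and 24 months. The same section schedules children aged 6–18 at baseline, 6, 12 and 24 months, and children under 6 every six months.

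On comparators, the Research design section states: "Cerebral Palsy Alliance will act as a comparison site as the tailored intervention is mandated in that organisation and embedded in routine practice". Overall purpose and hypotheses asks whether time trends show fewer adverse outcomes (severe scoliosis, hip dislocation, progressive limb contractures) among consenting children. If so, it asks: "are these trends comparable to Swedish cerebral palsy follow-up outcomes".

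The sample size section expects 614 children. It claims more than 90% power for a 10-point difference between baseline and later child measures when the baseline percentage is about 50%.

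**The concern.** The abstract's aim is causal: it credits routine assessment with any improvement. Answering it needs some account of how similar children would have fared over the same period without routine assessment. The planned child analysis is a trend within children who are all being assessed, and neither comparator in the article is unassessed.

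A falling trend could therefore not be credited to assessment, and a flat or rising one could not be held against it. The article looks to the findings to inform service decisions and funding, so a trend reported under the abstract's wording could be read as evidence that assessment works.

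**Working it through.** **1. Which contrast is powered.** Inputs from the sample size section: n = 614 children, p1 = 0.50, p2 = 0.60. The article states no alpha, so two-sided 0.05 is assumed. First, 0.80 × 768 = 614.4, which matches 614. Treating the two occasions as independent samples:

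- Pooled proportion = (0.50 + 0.60)/2 = 0.55
- SE under no difference = √(2 × 0.55 × 0.45 / 614) = 0.02839
- SE under the alternative = √((0.50 × 0.50 + 0.60 × 0.40) / 614) = 0.02825
- z = (0.10 − 1.96 × 0.02839) / 0.02825 = 1.57, so power = 94.2%

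A fall to 40% gives the same figure. A paired (McNemar) calculation with an assumed within-child correlation of 0 to 0.7 gives 94.1% to above 99.9%. The stated >90% is reproduced. It is power for later against baseline within assessed children. Power for assessed against unassessed cannot be computed, because the design has no unassessed group.

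**2. Candidate references for the child aim.**

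| Candidate | Where | What it supplies |
|---|---|---|
| Later visits of the same children | Outcome measures | Assessed; recorded by the intervention's own database |
| Fifth organisation | Research design | Assessed; the package is mandated there |
| Swedish follow-up | Overall purpose; Outcome measures | Assessed; described as a surveillance programme |
| Pre-implementation measures | Research design | Stated for clinician practices, not for child outcomes |
| Child's first assessment | Outcome measures; sample size section | A near-unexposed level at one time, not a course over time |

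Only the last row comes close to a before state. The sentence on musculoskeletal modelling does not name it, although the schedule (ages 6–18) and the power statement both do.

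**3. What a change from first assessment would contain.** Each child's 24-month visit falls about two years after the first. The change therefore combines two years of ageing and growth, two years of calendar time, other care, and all four intervention components. Hip dislocation and severe scoliosis develop over time, and the Background notes that displacement may progress. Their prevalence in a followed cohort could rise with age even if assessment helped.

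**4. How far age matching can help.** Assume entry ages are spread evenly over 3–18 and no child is lost.

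- Entry ages 3–18: 16 one-year bands
- Ages at 24 months: 5–20
- Overlap: ages 5–18, 14 bands; 14/16 = 87.5% of children can serve on each side
- At first assessment the usable children entered at 5–18; at 24 months they entered at 3–16. Entry ages common to both are 5–16, 12 bands; 12/16 = 75% of children appear on both sides

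Matching on age removes the ageing problem for most children. It does not separate assessment from the other three components or from calendar time. A child aged 12 at 24 months entered at 10, so an adverse outcome already present at entry would be counted as if it arose in the programme.

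**The case against.** The study is openly an uncontrolled before-and-after design, and the article says it is not a controlled healthcare intervention. The operative child question is descriptive: it asks about time trends and a benchmark. The fifth organisation is there to study diffusion between organisations and is never offered as a control for child outcomes. The article also promises pre-specified analysis plans for each question, so the handling of age may be settled there.

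Most of this stands. It places the fault in the abstract's causal wording, which goes beyond the research question, and it means the fifth organisation is not misused. It does not make the abstract's aim answerable, and an unseen analysis plan cannot supply a comparator the design lacks. Nor does it explain why the modelling sentence omits a baseline that the schedule and the power statement rely on.

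A reader might go further and infer that the design contains no before state at all. The documents do not support that. A baseline assessment is scheduled for ages 6–18, and the power statement is built on baseline against later. The database's feedback concerns change on reassessment, so it cannot have influenced a first measurement. What is missing is a course over time without assessment.

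**Conclusion.** The point holds as a mismatch between the stated aim and the design. The child data can describe trends in routinely assessed children and relate outcomes to time in the programme. They cannot establish that routine assessment improves outcomes. As written, the musculoskeletal model also leaves out the only near-unexposed measurement.

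The planned size is adequate for change over time on the article's own inputs (94.2%, alpha assumed). No figure can be attached to the effect of assessment itself.

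A reader might also infer that age matching would rescue the causal aim. It would not: the contrast concerns the whole package and assumes little routine assessment before entry and no strong cohort or calendar effects. The article gives grounds for caution on the first of these, since hip surveillance guidelines date from 2008 and their uptake is unknown. The 87.5% overlap rests on even entry ages and no loss to follow-up, neither of which the article gives.

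**What to change.** 1. Reword the abstract's child aim to match the research question: to describe trends in child outcomes under the multi-strategy programme and their association with time in the programme, with no claim that assessment improved outcomes.
2. Reconcile the modelling sentence under Outcome measures with the assessment schedule and the power statement, so that the first (baseline) assessment enters the child model. State what counts as the first assessment for children under 6, for whom no baseline is named.
3. As a supporting analysis in the four implementing organisations only, compare children of the same age and severity at first assessment with those at 24 months. Exclude, or count separately, adverse outcomes already present at entry, and allow for the correlation from children who appear on both sides. Report it as an association with the whole package, with the assumptions above.

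The cost is wording and analysis time, plus a more modest claim. The supporting analysis needs baseline musculoskeletal data, so their availability should be confirmed. The change was still possible when the article was written: database extraction, data cleaning and analysis had not begun.

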**Discussion:**

Government, policy makers and service providers all seek evidence-based information to support decision-making about how to distribute scarce resources, and families are seeking information to support intervention choices. This study will provide knowledge about what constitutes an efficient, evidence-informed service and which allied health interventions are implemented for children with cerebral palsy.

**Trial registration:**

Trial is not a controlled healthcare intervention and is not registered.

## Background

Children with cerebral palsy have a ‘permanent disorder of the development of movement and posture, causing activity limitations that are attributed to non-progressive disturbances that occurred in the developing fetal or infant brain. The motor disorders of cerebral palsy are often accompanied by disturbances of sensation, perception, cognition, communication and behaviour, by epilepsy and by secondary musculoskeletal problems’ [1]. Cerebral palsy is the most common cause of physical disability in childhood, with a prevalence of approximately 2.0 per thousand live births [2]. In 2007, it was estimated that 33,797 people with cerebral palsy were living in Australia [3]. Recent research has found that children with cerebral palsy may receive ineffective interventions despite numerous systematic reviews that report on the efficacy of specific therapeutic interventions in this population [4,5]. This finding is consistent with other research that shows between 10% and 40% of all patients do not receive treatments that have demonstrated high levels of effectiveness, and more than 20% of patients receive ineffective or harmful treatments [6]. It is therefore apparent that a research-practice gap exists in healthcare and specifically in relation to allied health professional (AHP) management of children with cerebral palsy.

One pertinent example of the consequences of a research-practice gap in the management of children and young people with cerebral palsy is the development of secondary musculoskeletal deformities that are a common feature of the condition. These deformities can include hip dislocation, which may result in pain, contractures and problems with functional activities such as walking, fractures, skin ulceration and difficulty with perineal care, pelvic obliquity and scoliosis [7]. In Australia, the overall incidence of hip displacement, which may progress to dislocation, is 35% in children with cerebral palsy [8]. While Australian hip surveillance guidelines were initially published in 2008 [9], and revised more recently [10], there is currently no knowledge as to whether there has been uniform adoption of these guidelines and no consistent mechanism for assisting AHPs to implement this evidence-based management approach. There is evidence that hip displacement can be detected for children who are enrolled in a surveillance programme [11-13]. Once detected, an opportunity exists for further active management, including consideration for surgery. Earlier detection of progression of hip displacement has been shown to lead to successful outcomes following surgery [7] and the abolition of salvage surgery [7,13]. Severe orthopaedic deformities among children with cerebral palsy have been almost eliminated in Sweden as a result of the implementation of a consistent surveillance programme and responsive surgery [13-16]. Successful surveillance provides an opportunity for more effective management of the musculoskeletal deformities associated with cerebral palsy and can reduce the significant consequences of ‘late referral’ such as the cost to children and families in receiving ineffective assessment or treatments and the cost to the tax payer of delivering an inadequate or ineffective service.

Knowledge translation is required to close the ‘research-practice gap’ [17] for children with cerebral palsy. It is defined as ‘the exchange, synthesis and ethically sound application of knowledge…to accelerate the capture of the benefits of research for [people] through improved health, more effective services and products, and a strengthened health care service’ [18]. Research utilisation and implementation describe the processes and actions by which specific research is implemented or executed within practice [18].

A number of barriers to implementing research evidence in clinical practice have been identified [19,20] which relate to the individual health practitioners, their workplace, their educational experiences and their patients [21]. In particular Haines et al. [19] and Sitzia [22] identified that:Individual practitioner barriers included obsolete knowledge, influence of opinion leaders who may go against research evidence and personal beliefs and attitudes, including a perception among many health professionals that they lack the authority to change clinical practice [20].Workplace barriers included a lack of financial and human resources, policies that did not promote cost-effective interventions or advocated unproven interventions, lack of access to evidence-based data, time limitations and a lack of disease registers.Educational system barriers included a failure of curricula to reflect current research evidence, inappropriate continuing professional development or education and a lack of incentives to participate in effective educational activities.Patient barriers included demands for care that is ineffective and perceptions or cultural beliefs about appropriate care.

Educational strategies have been traditionally used with the aim of bridging the research-practice gap. Such strategies include provision of educational materials, promoting attendance at conferences and professional development courses, establishing interactive small-group meetings within departments, use of opinion leaders and feedback on performance [6,19,20]. In spite of the diverse range of practical and applied strategies detailed above, systematic reviews have consistently shown that these approaches induce only a 6% improvement in health professionals’ evidence-based practice knowledge and have little influence on how AHPs actually practice [19,23,24]. Education or single strategies alone have been thought to be insufficient for changing the behaviour of health professionals in implementing research evidence [25-27], and tailored, complex interventions that seek to redress workplace barriers to research implementation have been recommended [19,28-30]. Other recommended strategies include (a) information technology support through the introduction of computers into practice to enable access to online evidence summaries and computerised decision supports to link individual health information with health knowledge to aid clinical decision-making [6,19,20,31] and (b) workplace alterations such as encouraging multi-professional collaboration, fostering a research culture and quality management or improvement strategies [19,20,31]. More recently, a systematic review of systematic reviews, published after the initiation of this trial, concluded that the evidence for multifaceted interventions, compared to single-component interventions, in changing healthcare professionals’ behaviours was not compelling [32]. No statistical evidence of a relationship between the number of interventions provided and the effect size was observed; however, the review commented that methods of categorising intervention elements were not transparent, and so delineation between ‘single’ versus multifaceted interventions may be difficult [32].

A single-blind clustered randomised controlled trial (RCT) has investigated the effect of a tailored complex intervention on the research implementation of AHPs that work with children with cerebral palsy in a single organisation [33]. The tailored multifaceted intervention comprised (a) redressing workplace barriers in partnership with knowledge brokers and (b) providing a customised intranet resource consisting of an e-evidence library of synthesised and critiqued cerebral palsy research, a suite of decision-making intervention algorithms based on best available evidence and the latest research on cerebral palsy prognosis and assessment. The study demonstrated statistically significant differences between the intervention and control groups in evidence-based practice knowledge. Improvements in self- and peer-rated evidence-based practice behaviours were found for the intervention group relative to the control group; however, the difference was not statistically significant after adjusting for the clustering effect [33]. Campbell and colleagues [31] demonstrated that a specific package of strategies may improve knowledge and behaviour in a particular organisation; however, it is not known whether the strategies can effectively be applied across varying organisations within the health and disability sector.

This paper describes the study protocol for a partnership project funded by the National Health and Medical Research Council of Australia. The ethically approved project title is *Cerebral palsy check up: providing the best service at the best time.* This paper describes the rationale and methodology for a ‘real-world’ implementation study that aims to improve evidence-based practice behaviours of AHPs that work with children with cerebral palsy via the application of a tailored multi-strategy knowledge translation intervention. The intervention will be applied pragmatically in ‘real-world’ settings in different disability service organisations in Australia.

